## 1. Introduction

Coronary heart disease (CHD) is the leading cause of death worldwide, with more than 1.5 million deaths each year [1, 2]. Aspirin is a well-known baseline antiplatelet agent, serving as the first choice for the prevention and treatment of CHD. However, many studies have shown that the long-term administration of aspirin has the potential for significant side effects on the gastrointestinal tract causing mucosal lesions, bleeding, or peptic ulcers [3]. Although enteric-coated aspirin have been developed, 10%–25% long-term users still got peptic ulcers [4] and aspirin increases the risk of gastrointestinal bleeding by almost 3-fold [5]. These side effects limit the regularity of medication which increases the risk of cardiovascular accidents. Therefore, it is particularly important to prevent the occurrence of aspirin-induced gastrointestinal injury. While proton pump inhibitor (PPI) preparations are usually recommended to prevent aspirin-induced gastrointestinal injury [4], especially for the elderly, the application of PPI damages the phospholipid layer in intestinal mucus, which may protect gastric mucosa but increase the risk of small intestinal injury [6]. Therefore, it is urgent to find a strategy to reduce aspirin-induced gastrointestinal injury.

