## 2. Methods

### 2.1. Study Design and Setting

This is a prospectively planned, open-labeled, parallel-grouped, single-centered clinical trial. The trial will be conducted at the outpatient care of the Cardiology Department at the Dongzhimen Hospital, Beijing University of Chinese Medicine in China. The staff of the department will be informed of the trial and they will help researchers to recruit participants. The trial is conducted by the ethical principles laid down in the Declaration of Helsinki, the Guideline for Good Clinical Practice, and local laws. The informed consent form will be obtained from all participants before any trial-related procedures were conducted, enrolled after a complete and extensive description of the study. The trial was approved by the Ethics Committee of Dongzhimen Hospital, Beijing University of Chinese Medicine (Supplementary File 1). We present the protocol in accordance with the SPIRIT reporting checklist (Standard Protocol Items Recommendations for Interventional Trials) (Supplementary File 2).

In terms of research methods, we refer to and improve one of our previous experimental designs [14]. 480 participants will be randomly assigned to either an aspirin group, a Xuesaitong group, or drug combination group at a ratio of 1: 1: 1. Participants in the aspirin group will be administered aspirin (100 mg, qd) orally 30 min after breakfast, participants in the Xuesaitong group will be administered Xuesaitong soft capsule (contains PNS and excipients; 200 mg, tid) orally 30 min after breakfast, and participants in the drug combination group will be administered both drugs above. The two drugs should be taken half an hour apart, and aspirin should be taken first. All treatment courses will last for 30 days. Blood samples will be acquired 30 min before administration on day 1 and 30 min after administration on day 30. The volume of each blood sample is 4 mL. And fecal samples will be collected on days 1 and 30. Details of patient follow-up are summarized in Table 1 and Figure 1.

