### 2.6. Combination

Participants are not allowed to take any kind of herbal or chemical medication which have the pharmacological effects of activating blood circulation, preventing platelet aggregation, or anti-inflammatory activityParticipants with angina pectoris could take isosorbide mononitrate. In addition, participants could take other medications that have no known drug-drug interaction with aspirin or Xuesaitong soft capsule

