## Figures and Tables

**Figure 1 fig1:**
[figure not shown]
A schematic flowchart of the clinical trial.

**Table 1 tab1:** Flowchart of a patient follow-up

Group	Screening D-7 to D1	D1	D30	D31 closeout
Patient information	X			
Physical examination	X	X		X
Vital signs	X			X
Blood routine; serum biochemistry; urine routine; stool routine; coagulation routine	X^1^	X^1^		X^1^
ECG	X			X
Stool biomarkers (calprotectin; I-FABP)		X	X	
Blood biomarkers (platelet aggregation; P2Y12; PAC-1; P-selectin)		X	X	

D: day; ECG: electrocardiogram; I-FABP: intestinal fatty acid-binding protein; PAC-1: platelet-associated complement 1. ^1^If the abnormality of this program is clinically significant, if it occurs before screening and at baseline, the subjects will be excluded directly. If it occurs during the observation period of administration, the retest will be followed up until the examination is normal or the abnormality is considered by the study doctor to be of no clinical significance.

**Table 2 tab2:** Inclusion, exclusion, and termination criteria.

Criteria
*Inclusion criteria*
(1) 45–75 years of age without gender restriction
(2) Meet the diagnostic criteria of CHD
(3) Meet the diagnostic criteria of grade I–II angina
(4) Meet the diagnostic criteria of blood stasis
(5) Meet the diagnostic criteria of stable angina pectoris
(6) Take regular aspirin (enteric-coated) for at least one year (the incidence of bleeding events, adverse events (AEs), and adverse reactions will be noted)
(7) Calprotectin in stool is above 50* μ*g/g
(8) Before the study start, patients and their families are fully informed and voluntarily willing to sign an informed consent

*Exclusion criteria*
(1) Mental or physical disorders
(2) Pregnant, menstruating, and breastfeeding women
(3) Severe heart disease and severe cardiopulmonary dysfunction
(4) Severe primary diseases, such as cancer, liver and renal damage, and multiple organ failure
(5) Poorly controlled hypertension (>160/100 mmHg)
(6) Current participation in another clinical trial or participation in another clinical trial within three months
(7) Having underwent surgery within eight weeks
(8) Having drug allergy history or allergic constitution
(9) Diabetes
(10) Status epilepticus
(11) Unstable vital signs
(12) Combined with serious infection, infectious diseases
(13) Acute intestinal infection
(14) Unsuitability or poor compliance for this trial

*Termination criteria*
Participant termination

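### Table 2 as shown lets a now-stable patient with a recent coronary event or stent be randomised, with a 1 in 3 chance of 30 days on Xuesaitong without aspirin; one named exclusion would close the gap.

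*Protocol article*

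**What the plan says.** **Who enters.** Section 2.2 refers to Table 2 for the detailed criteria. Patients must have coronary heart disease, grade I–II angina and stable angina ("5) Meet the diagnostic criteria of stable angina pectoris"), and must be long-term aspirin users ("6) Take regular aspirin (enteric-coated) for at least one year").

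**What they receive.** Section 2.1 randomises 480 patients 1:1:1. In one arm, "participants in the Xuesaitong group will be administered Xuesaitong soft capsule". Table 3 lists no aspirin for that arm, and treatment lasts 30 days.

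**What else they may take.** Section 2.6 states: "Participants are not allowed to take any kind of herbal or chemical medication which have the pharmacological effects of activating blood circulation, preventing platelet aggregation". It does not say how this applies at entry to someone already using a second antiplatelet drug.

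**Which exclusions touch coronary risk.** Four of the 14 do: "3) Severe heart disease and severe cardiopulmonary dysfunction", "7) Having underwent surgery within eight weeks", unstable vital signs (11), and "14) Unsuitability or poor compliance for this trial". Table 1 adds an ECG and laboratory tests at screening.

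**The concern.** For one third of the participants the trial replaces a long-standing antiplatelet treatment. How safe that is depends on coronary history as well as on present symptoms. The criteria shown describe present symptoms (stable, grade I–II) and general severity. They do not ask when the patient last had an infarction, an acute coronary syndrome or a coronary procedure.

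The Introduction shows that the authors regard interrupted treatment as a risk. Of aspirin's gastrointestinal side effects it says: "These side effects limit the regularity of medication which increases the risk of cardiovascular accidents". That sentence concerns long-term adherence, so it does not measure the risk of a supervised 30-day substitution. It does show why entry to the aspirin-free arm should follow a written rule for patients with a recent event or stent.

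What is at stake is patient safety at entry. The planned comparisons, the error rate and the power are not affected.

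**Working it through.** **1. Chance of the aspirin-free arm.** Inputs from section 2.1: 480 participants, ratio 1:1:1.
- Arm size: 480 × 1/3 = 160, which agrees with the 160 in section 2.4.
- Chance for any randomised patient: 160/480 = 1/3.

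**2. Absence of aspirin in that arm.** Table 3 gives Xuesaitong 200 mg t.i.d. only, and section 2.6 bars other drugs that prevent platelet aggregation. Together they mean no aspirin for 30 days.

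**3. Test cases against Table 2.** Each patient below has coronary heart disease, has taken aspirin for over a year, and now has stable grade I–II angina.
- *Stent nine weeks ago, catheter procedures counted as surgery.* Exclusion (7) no longer applies, since nine weeks exceeds eight. No other criterion names the stent.
- *Stent four weeks ago, catheter procedures not counted as surgery.* Exclusion (7) does not apply at any interval.
- *Infarction or acute coronary syndrome treated with drugs only.* There was no procedure, so exclusion (7) is irrelevant.
- *Currently on a second antiplatelet drug.* No exclusion names this. The patient cannot comply with section 2.6, so the natural outcome is refusal under exclusion (14). That outcome is inferred and not written.

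In the first three cases the patient is kept out only if the investigator judges that exclusion (3) or (14) applies, if vital signs are unstable, or if the unseen definition of stable angina sets an event-free period. The one-year aspirin rule is a further, indirect filter: a patient who began aspirin at the coronary event must be a year past it. It does not filter someone who was already on aspirin when the event occurred.

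**4. Number affected.** The expected number in the Xuesaitong arm is 160 × p, where p is the share of randomised patients who have such a history and have passed every existing criterion. The documents give neither p nor anything from which to estimate it, so they bound the count only between 0 and 160. The conclusion does not need a value for p, and none is assumed.

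**5. What the protocol offers in place of aspirin.** The Abstract says that Xuesaitong inhibits platelet aggregation in coronary patients. Section 2.4 plans on aggregation of 37.79% with Xuesaitong against 38.72% with aspirin, a difference of 38.72 − 37.79 = 0.93 percentage points. These are platelet-function measures. The good clinical effect mentioned in the Introduction is for use together with aspirin. Section 2.5 and the Discussion mention established cardiovascular use but give no clinical outcome figure for Xuesaitong alone.

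**6. Later safeguards.** Section 2.9 provides adverse-event review and a DSMB, and Table 2 allows participant termination. Table 1 schedules no assessment between day 1 and day 30, and the follow-up ECG is at day 31. All of these act after randomisation.

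**The case against.** **The article condenses a fuller protocol, and the deciding definition is unseen.** Table 2 refers to diagnostic criteria for stable angina without reproducing them, and those may already require an event-free period. This stands as a limit on the conclusion. It does not remove the point, because section 2.2 presents Table 2 as the detailed list. That list is specific on other matters, with a blood-pressure threshold, an eight-week surgery window and a three-month rule on other trials.

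**Existing criteria and cardiology judgement already filter.** Recruitment is through a cardiology department, and exclusions (3), (7), (11) and (14) may keep many of these patients out. This is accepted. What remains is that protection depends on individual judgement where a rule would be simple.

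**Xuesaitong is itself presented as antiplatelet.** This is true and is the stated rationale for the arm. A reader might infer that 160 patients are left without any antiplatelet effect; the documents do not support that. They do leave the rationale resting on surrogate measures, which is thin support for the patient with a recent event or stent.

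**No second antiplatelet drug is said to be stopped.** A reader might infer from section 2.6 that such a drug would be withdrawn to allow entry. The documents describe no such withdrawal, and section 2.6 read with exclusion (14) points to refusal. On this part the request is only to write the rule down.

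**Conclusion.** The point holds as a patient-safety improvement to the entry criteria. As shown, Table 2 does not exclude by name a now-stable patient with a recent infarction, acute coronary syndrome or stent. Such a patient, once randomised, has a 1 in 3 chance of 30 days without aspirin. The existing criteria cover this in part and by judgement.

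The conclusion assumes that the stable-angina definition sets no event-free period. If it does, the point reduces to carrying that period into Table 2.

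Two further inferences are not supported. The arm size of 160, or that number multiplied by 30 days, describes the three-arm design and does not measure the gap, which concerns an unknown subset. Nor do the documents allow any statement about excess cardiac events or about bias in the trial's results.

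**What to change.** Add one exclusion to Table 2, checked before randomisation and applied in all three arms:

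*Current use of, or indication for, a second antiplatelet drug (not to be stopped to allow entry); or myocardial infarction, acute coronary syndrome or coronary revascularisation, including PCI, within [window].*

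The sponsor's cardiologists should fix the window. It should be no shorter than the eight weeks in exclusion (7), and their choice may well be longer. Section 2.6 should refer to this exclusion, so that the drug ban is read as an entry rule. If the stable-angina definition or a fuller protocol already sets a window, carry it into Table 2.

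The cost is a protocol amendment of one line and a cross-reference, plus a history question at screening. The population becomes slightly narrower and recruitment may slow. Sample size, visits and assays do not change.

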## Data Availability

The datasets used and analyzed in the current study are available from the corresponding author on reasonable request after the study completion.

## Abbreviations

PNS: Panax notoginseng saponins
CHD: Coronary heart disease
PPI: Proton pump inhibitor
AUC: Area under the curve
I-FABP: Intestinal fatty acid-binding protein
PAC-1: Platelet-associated complement 1
ECG: Electrocardiogram
CCS: Canadian Cardiovascular Society
DSMB: Data and Safety Monitoring Board
HR: Hazard ratio
CI: Confidence interval
VEGFA: Vascular endothelial growth factor A.
